### Trial design

The Chimney Trial is designed as a prospective, randomized, controlled, multicenter, single-blinded study of patients who had undergone either mini-invasive laparoscopic and robotic-assisted APR or low Hartmann’s procedure for rectal adenocarcinoma. The trial is independent from any kind of industrial sponsorship.

Previous research on PVDF mesh used for PSH prevention is scarce. We conduct and evaluate the complications and adverse events of PVDF mesh for safety reasons for 30 patients who have completed 30 days’ follow-up in a group with the mesh and another group with a conventional colostomy without a mesh. If there are 10% or more serious complications defined by Clavien-Dindo classification 3B in either group, the trial will be regarded as unethical and will be terminated. For the same safety reasons, there will be further analyses on the effectiveness and complications when 30 patients in both groups have reached the 1-year follow-up. If the PSH rate is increased by more than 35% in the control group compared with the PVDF-mesh group or there are 10% or more complications defined by Clavien-Dindo classification 3B in either group compared with the other group, the trial will be terminated as unethical to continue. In case of terminating the trial prematurely, the data collected and potential complications are published.

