As current results from the use of the most evaluated keyhole technique in PSH prevention are unsatisfactory, more trials are needed to define the efficiency and safety of other methods to prevent PSH. As previous research on the PVDF mesh used in this trial is limited, there are clearly predefined safety limits of PSH incidence and complications to determine when to prematurely finish the trial as unethical to continue. For the same reason, the trial is designed to compare the mesh group to control group without any mesh to detect the objective efficiency and safety of funnel-shaped PVDF mesh. Since there is a lack of long-term results of PSH prevention, the sample size is estimated to reach statistically significant results at the long-term follow-up at 5 years.

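### The only hernia limit at the 1-year look is a stop for mesh benefit, although the protocol presents it as a safety limit adopted because the mesh is little studied

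*Protocol article*

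**What the plan says.** The Trial design section plans two looks, and gives as background that "Previous research on PVDF mesh used for PSH prevention is scarce".

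- **30-day look.** There is a complication limit only: "If there are 10% or more serious complications defined by Clavien-Dindo classification 3B in either group".
- **1-year look.** This takes place "when 30 patients in both groups have reached the 1-year follow-up" and is introduced with "For the same safety reasons, there will be further analyses on the effectiveness and complications". The hernia limit is "If the PSH rate is increased by more than 35% in the control group compared with the PVDF-mesh group". The complication limit in the same sentence is "10% or more complications defined by Clavien-Dindo classification 3B in either group compared with the other group".

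The Discussion, after noting that research on this mesh is limited, states that "there are clearly predefined safety limits of PSH incidence and complications to determine when to prematurely finish the trial as unethical to continue".

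The article gives no PSH limit for the case in which the mesh arm does worse.

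**The concern.** A limit justified by how little is known about a device would be expected to respond when the device does badly. This one looks only at an excess in the control arm. Both complication limits are worded for either group, so the hernia limit is the only one of the three that runs in a single direction.

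The property at stake is the one the Discussion claims: that PSH incidence, the basis of the primary outcome, has a predefined limit that protects patients from a scarcely tested mesh. If the mesh increased hernias, the investigators could see this at the 1-year look, but no written rule would tell them to stop. Under even accrual some tens of mesh implants would still be ahead at that point, so a rule acting then would still matter.

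**Working it through.** **Inputs.** There are 30 patients per arm at the look (Trial design). Planning PSH rates at 12 months are 6.4% with mesh and 34% in controls (Sample size). The total is 204 patients (102 per arm), allocated 1:1, with enrolment over about 2 to 3 years (Recruitment). The article does not say whether 35% is absolute or relative, so both readings are run. Mesh rates above 34% are assumptions; the article gives no harmful rate for this mesh.

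**The plan's own figure.** The sample size is not in dispute. For 6.4% versus 34%, two-sided α = 0.05 and 90% power, the continuity-corrected formula gives 50 per group against the stated 51. The inflation 51 / (1 − 0.5) = 102 is exact.

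**Step 1: which results can trigger the written limit.** Let m and c be the numbers of hernias among 30 mesh and 30 control patients.

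- Absolute reading: (c − m)/30 > 0.35, which needs c − m ≥ 11.
- Relative reading: c > 1.35 × m.

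There are 31 × 31 = 961 pairs (m, c). Those with m ≥ c number 31 × 32 / 2 = 496. None of the 496 meets either condition.

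**Step 2: how often it triggers.** The chance is the sum, over triggering pairs, of Bin(m; 30, mesh rate) × Bin(c; 30, control rate), with the control rate at 34%.

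| True mesh rate | Absolute reading | Relative reading |
|---|---|---|
| 6.4% (planning) | 22.2% | 99.0% |
| 34% (equal) | 0.2% | 20.6% |
| 50% | 0.003% | 1.3% |
| 60% | <0.001% | 0.10% |
| 70% | about 0 | about 0 |

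The triggers in the last three rows are samples in which controls happened to look worse by chance. The limit is most active when the mesh works, which is how a benefit stop behaves.

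**Step 3: what a mesh-worse limit could do (illustration).** Trigger if the one-sided Fisher exact p is below 0.025 in the direction of more hernias with mesh, 30 per arm, control rate 34%.

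| Assumed true mesh rate | Chance of stopping |
|---|---|
| 40% | 4.0% |
| 50% | 16.6% |
| 60% | 43% |
| 70% | 74% |

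With equal rates in both arms anywhere from 6.4% to 34%, the false-stop chance is at most about 1.3%. With 10/30 control hernias, the limit needs at least 19/30 in the mesh arm.

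**Step 4: patients still to come at the look.** Assume even accrual, the first 60 patients split 30/30, and no losses. The look then falls at (60/204) × T + 12 months.

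- T = 24: 7.1 + 12 = 19.1 months. Enrolled by then: 204 × 19.1/24 = 162. Remaining: 42, of which 21 mesh.
- T = 36: 10.6 + 12 = 22.6 months. Enrolled by then: 204 × 22.6/36 = 128. Remaining: 76, of which 38 mesh.

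**The case against.** A one-directional limit is not in itself an error. Stopping when controls do much worse protects control patients from being denied an effective mesh, which fits the stated ground that continuing would be unethical. Grade 3B complications are serious in either arm, whereas the Introduction says many PSHs are asymptomatic, so the two outcomes may reasonably have different limits. This stands: the defect is the mismatch between the rule and its description, not the asymmetry alone.

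The complication limit runs in both directions and would catch mesh harm where hernias lead to grade 3B events. That is partial cover. It would miss asymptomatic hernias seen only on CT, which the primary outcome counts, and it is not a limit on PSH incidence.

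Nothing the article cites suggests that mesh nearly doubles hernias. It reports 6.4% for this mesh in a case series, and 32% with against 34% without a retromuscular mesh in a randomized trial. So 60% to 70% is a severe assumption, and for moderate harm the illustrative limit delivers little. This stands too, and is why the 40% and 50% results are shown beside the others.

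A reader might infer that the trial would be obliged to go on implanting a harmful mesh. The article does not support that: it plans an analysis of effectiveness at this look, does not say that the listed limits are the only grounds for stopping, and condenses a fuller protocol that is not shown. A reader might also infer that the rule can never trigger when the mesh is truly worse. That is exact for observed results only; on the relative reading, chance reversal triggers it in 1.3% of trials at 50% versus 34%.

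**Conclusion.** The point holds as a mismatch between the rule and what is said about it. The only PSH limit triggers solely on an excess in controls, and no observed result with as many or more hernias in the mesh arm can trigger it, on either reading of 35%. This part rests on the wording and on enumeration, and needs no assumed rates. The Trial design section nevertheless gives safety as the reason for the look, and the Discussion describes a safety limit on PSH incidence motivated by limited research on the mesh. That property is not delivered: no predefined rule calls for stopping if the mesh increases hernias.

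The practical size depends on assumption. Under even accrual, about 21 to 38 mesh implants would follow the look. A mesh-worse limit of the kind illustrated guards against large harm only. The documents do not establish that a harm boundary is required; they establish that the rule and its description must be brought into line.

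**What to change.** Reconcile the Trial design section with the Discussion in one of two ways.

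1. Add a predefined PSH limit for the mesh-worse direction at the same 1-year look. The one-sided Fisher p<0.025 limit above is an illustration; the threshold is the sponsor's to choose and justify. It uses data already tabulated at that look. Because it stops only when the mesh does worse, it does not inflate the error of a claim of mesh benefit. The cost is one sentence in an amendment and about a 1% chance of a false stop (at most about 1.3%).
2. Call the present rule a benefit limit in Trial design, and remove PSH incidence from the safety limits claimed in the Discussion. This has no statistical cost, but leaves hernia harm from the mesh without a predefined rule.

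In either case, state in the same sentence whether 35% means percentage points or a relative increase.

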## Methods/design

### Study setting

This study is a multicenter study involving several Nordic hospitals. Hospitals currently participating in this study are Oulu University Hospital, Helsinki University Hospital, Turku University Hospital, Tampere University Hospital, Jyväskylä Central Hospital, and Seinäjoki Central Hospital in Finland and Västmanlands Hospital Västerås in Sweden. It is expected that hospitals from other Nordic countries, such as Norway and Denmark, will join the trial later.

Oulu University Hospital and Seinäjoki Central Hospital began recruitment in February 2019 with other hospitals soon to following.

### Eligibility criteria

All patients who fulfill the inclusion criteria without meeting any of the exclusion criteria are considered to participate in the trial at any of the hospitals during the study period (Fig. 1). Patients are enrolled in the study in the outpatient department at a visit prior to surgery. All patients who undergo APR or Hartmann’s procedure for rectal adenocarcinoma during the study period in each attending hospital are recorded without identification details for later analysis of selection biases.

**Fig. 1 Fig1:**
[figure not shown]
Flow chart

If a patient refuses to attend the trial, they are treated according to routine practice.

### Inclusion criteria

APR or low Hartmann’s procedure for rectal cancer with curative intent and permanent end colostomy, either by laparoscopic technique or robotic-assisted APR18 years of age or olderPatient has a life expectancy of at least 12 monthsPatient signs the informed consent and agrees to attend all study visits

### Exclusion criteria

APR or Hartmann’s resection by laparotomy or conversion to laparotomyComplications requiring laparotomy during postoperative treatment on the surgical wardPatient with a comorbid illness or condition that would preclude surgical treatment (American Society of Anesthesiologists (ASA) 4–5)Patients with concurrent or previous malignant tumors within 5 years before study enrollmentPatients with grade-T4b tumors that impose a multi-organ resectionRectal malignancy other than adenocarcinomaPatients undergoing emergency proceduresPlanned rectal surgery along with major concomitant procedures (e.g., hepatectomies, other intestinal resections)Metastatic disease with no possibility of curative surgeryPregnancy or suspected pregnancyPatients living geographically distant and/or unwilling to return for follow-ups or comply with all study requirementsActive abdominal infection at the time of surgeryPrevious surgery at the colostomy siteLanguage barrier or other reasons why informed consent is not possible

### Interventions

Perioperative care includes the assessment and optimization of medical risk factors, thromboprophylaxis with low-molecular-weight heparin and elastic antiembolic stockings, standard anesthesia and the avoidance of hypothermia. Antibiotic prophylaxis and mechanical bowel preparation are accomplished according to the hospital protocol. Postoperative treatment on the surgical ward is accomplished according to standard enhanced recovery after surgery (ERAS) protocols.

### Surgical technique

PVDF mesh (DynaMesh®-IPST, FEG Textiltechnik GmbH, Aachen, Germany) is placed on the intraperitoneal surface as described by Berger et al. [22], Conde-Muino et al. [23] and Köhler et al. [24]. The bowel forming the colostomy is closed with a linear-stapling device. The trephine is created by excision of the skin at the site previously marked by a trained ostomy nurse. Subcutaneous tissue is not excised. A cross-shaped incision is made to the anterior rectus sheath. The rectus abdominis muscle is split in the direction of the fibers, and the posterior rectus sheath is opened longitudinally. A 15 × 15-cm mesh with a tube length of 4 cm and a width of 2 cm is used (Fig. 2). The tube is stretched using the surgeon’s fingers to match the diameter of the bowel (Fig. 3). The bowel is brought through the orifice and then through the saline lubricated tube in the PVDF mesh (Fig. 4). The mesh is translocated into the intra-abdominal space with the funnel oriented dorsally and fixed in the intraperitoneal onlay position by absorbable tackers (Securestrap™, Ethicon) using the double-crown technique as described and pictured previously by Köhler et al. [24] (Fig. 5) The corners of the mesh are fixed first, then the tackers are attached every 2 cm on the outer row. The inner row is fixed at 12, 3, 6, and 9 o’clock positions. The stoma is fixed and everted with absorbable monofilament sutures to the skin just above the skin level. A catalog of the operative technique will be sent to all participating surgeons to standardize the procedure.

**Fig. 2 Fig2:**
[figure not shown]
The polyvinylidene difluoride (PVDF) mesh (DynaMesh®-IPST, FEG Textiltechnik GmbH, Aachen, Germany) with the 4-cm long funnel

**Fig. 3 Fig3:**
[figure not shown]
The funnel-shaped tube is stretched with fingers to match the diameter of the bowel

**Fig. 4 Fig4:**
[figure not shown]
The bowel is brought through the funnel oriented dorsally

**Fig. 5 Fig5:**
[figure not shown]
The polyvinylidene difluoride (PVDF) mesh is attached to the abdominal wall using absorbable tackers

In the control group, the colostomy is formed by the identical method as described above. The only difference is that there will be no mesh.

### Outcomes

The primary endpoint of this study is the incidence of PSHs, either symptomatic or asymptomatic, detected by a CT scan during the 12 months’ post-surgery follow-up. A CT scan with the Valsalva maneuver being performed is performed at the 1-year and 3-year follow-up after rectal adenocarcinoma operation as a part of routine follow-up protocol and to detect the incidence of radiological PSHs. All patients are also assessed at each follow-up point (Table 1) by an experienced surgeon to detect clinical PSH or complication of stoma as secondary outcome. There will be clinical evaluation without CT scan to detect any clinical PSH as long-term follow-up at 5 years after surgery.

**Table 1 Tab1:** Participant timeline

Schedule of events	Baseline	Procedure	Discharge	30 days ±3 days	1 year ±14 days	3 years ±30 days	5 years ±30 days	Unscheduled visit
Informed consent	X							
Demographics and medical history	X							
QoL (RAND-36)	X			X	X	X	X	
QoL (colostomy impact score)				X	X	X	X	
Procedure details		X						
CT scan findings					X	X		
Protocol deviation	X^a^	X^a^	X^a^	X^a^	X^a^	X^a^	X^a^	X^a^
Complications		X^a^	X^a^	X^a^	X^a^	X^a^	X^a^	X^a^
Study closure form							X^b^	

Legend: *CT* computed tomography, *QoL* quality of life

^a^Complete if applicable

^b^Complete when lost to follow-up, consent withdrawal or subject has completed all study-related visits

All CT scans are analyzed by two independent radiologists. Measurements are recorded of fascial defect at stoma, the size of any possible PSH sac and fascial defect of a hernia, the content of the hernial sac, the location of the stoma and other hernias. The hernias will be graded according to the European Hernia Society criteria [25].

Primary outcome
PSH, either symptomatic or asymptomatic, detected by CT scan during 12 months’ follow-up

Secondary outcomes
Incidence of CT-detected PSH during 3-year follow-upIncidence of clinically detected PSH during 1-, 3-, and 5-year follow-upsPSH-operation-free survival at 3 and 5 yearsSurgical-site infection (SSI) rateClavien-Dindo grade I–V complications at 30 days postoperativelyStoma-related complications and problems during long-term follow-upStoma-related readmissionsReoperation rateOperative timeLength of stay (LOS) in daysQuality of life (RAND-36, colostomy impact score)Medico-economic sub-study including direct costs at hospital and indirect costs caused by sick leaveRadiological sub-study including definition of abdominal wall measurements and location of stoma

### Radiological sub-study

Subcutaneous abdominal fat in centimeters on the contra-lateral side of the stomaDistance of the medial part of the stoma to midline (umbilicus as the midline definition)Area of the stoma aperture (2 cm width × height/2)

The SSI is defined and recorded per the Centers for Disease Control and Prevention (CDC) SSI definition [25].

Clavien-Dindo classification is utilized for complications. All related costs are analyzed in detail. The direct costs, including the meshes, resources and stay at the hospital, are monitored, and the indirect costs from losses of productivity are recorded.

### Pre-intervention data

AgeSexASA classWeight, heightOther illnesses and medicationsSmoking historyPrevious hernias, either symptomatic or asymptomaticNeoadjuvant treatmentPreoperative hemoglobin and carcinoembryonic antigen (CEA)Quality of life defined by the RAND-36Informed consent and patient informationRandomization

### Intervention data

Antibiotic prophylaxisOperating timeResources used during the operationTotal blood loss

### Post-intervention data

Length of postoperative ileus (POI) measured in days and defined by air in the stomaRe-operation rateComplications as defined by Clavien-Dindo classificationIncidence of SSI as defined by the CDCIncidence of either clinically or radiologically detected PSHsQuality of life at each follow-upProblems and complications with stomaTumor–nodes–metastases (TNM) scoreHemoglobin and CEA at each controlOncological adjuvant treatment given

All exceptions to the protocol are recorded and explained in detail at each time point.

### Sample size

To calculate a sample size needed to compare the two groups, we estimated a 6.4% rate of PSH and 34% PSH on a CT scan for the PVDF-mesh group and control group during 12 months’ follow-up [21, 23]. Assuming α = 0.05 and power = 90%, we would need 51 patients per group. Furthermore, assuming a 5-year drop-out rate of 50%, 102 patients per group are needed to reach statistically significant results also during long-term follow-up.

All analyses will be performed by, or under the guidance of, professional statisticians and following the Consolidated Standards of Reporting Trials (CONSORT) guidelines [26].

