**Methods/design:**

The Chimney Trial is a Nordic, prospective, randomized controlled, multicenter trial designed to compare the feasibility and the potential benefits of specifically designed, intra-abdominal onlay mesh (DynaMesh®-Parastomal, FEG Textiltechnik GmbH, Aachen, Germany) against controls with permanent colostomy without mesh.

The primary outcome of the Chimney Trial is the incidence of a PSH detected by a computerized tomography (CT) scan at 12-month follow-up. Secondary outcomes are the rate of clinically detected PSHs, surgical-site infection as defined by the Centers for Disease Control and Prevention (CDC), complications as defined by the Clavien-Dindo classification, the reoperation rate, operative time, length of stay, quality of life as measured by the RAND-36 survey and colostomy impact score, and both direct and indirect costs. For each group, 102 patients were enrolled at attending hospitals and randomized at a ratio of 1:1 by browser-based software to receive a preventive mesh or a conventional colostomy without a mesh. Patients will be followed for 1 month and at 1, 3, and 5 years after the operation for long-term results and complications.

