## Introduction

### Background and rationale

Abdominoperineal resection (APR) with permanent end-colostomy formation was introduced in the late twentieth century as a surgical method to treat distal rectal cancer in order to decrease the previously high incidence of local recurrence [1, 2]. Despite the rising trend of saving sphincter function, APR still remains the primary operation of choice for patients with low rectal cancer [3]. Even more, the low Hartmann’s procedure with permanent colostomy is increasingly performed in older and frailer patients who are not suitable for an anastomoses [4].

The reported incidence of parastomal hernias (PSHs) with permanent end colostomy rises to 81% after long-term follow-up [5]. Due to increased use of minimally invasive rectal cancer surgery and better survival, an increased incidence of PSHs might be expected [6, 7]. Many PSHs are asymptomatic, and clinical examinations can reveal only some of them compared with computed tomography (CT) scans [7, 8]. Most PSHs are diagnosed within 2 years after the construction of the stoma, but their incidence increases after longer follow-up [5, 9, 10].

The results of PSH repair are still unsatisfactory due to a high rate of complications [11]. Therefore, the initial focus should be on prevention, which is recommended in guidelines by the European Hernia Society [11].

Several randomized control trials (RCTs) and meta-analyses have shown positive results for synthetic meshes utilized as prophylaxis with various techniques and meshes [5, 6, 12–19]. Trials have demonstrated a lower incidence of PSHs without a higher risk of complications. However, despite the use of a prophylactic mesh, the incidence of PSHs has been surprisingly high. Clinically detected hernias are present in up to 10.6–16.4% of patients with a parastomal mesh, and the incidence of radiologically detected hernias is 32.4–36.6% on recent meta-analyses [18, 20]. Additionally, a recently published RCT [21] reported similar rates of radiologically detected PSHs at 1 year after open APR in patients with (32%) and without (34%) a prophylactic retromuscular sublay mesh.

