Polyvinylidene difluoride mesh (PVDF, DynaMesh®-IPST, FEG Textiltechnik GmbH, Aachen, Germany) is a synthetic mesh with a 4-cm-long, central, seamless tube (chimney) designed to repair and prevent PSHs. There are three case series [22–24] published on its use as a prophylactic mesh. In 2008, Berger et al. [22] found no clinically detectable hernias by CT scan at 1-year follow-up. In another trial, [23] the incidence of PSHs was clinically found 3.2% and in CT scans 6.4% at the 1-year follow-up in a case series of 31 patients. The prophylactic method was safe with no unexpected complications. No RCTs have been published so far. The design of the mesh with a central tube forming a stocking-like lining around the bowel may be crucial for PSH prevention [22] and blocking stomal-orifice enlargement occurring with keyhole techniques [13].

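### The sample size is said to give significant results at 5 years, but it was calculated for a 12-month CT endpoint that is not measured at 5 years

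*Protocol article*

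**What the plan says.** The Sample size section of the protocol article uses one pair of event rates: "we estimated a 6.4% rate of PSH and 34% PSH on a CT scan for the PVDF-mesh group and control group during 12 months’ follow-up". From these it concludes: "Assuming α = 0.05 and power = 90%, we would need 51 patients per group". It then doubles the number for attrition: "assuming a 5-year drop-out rate of 50%, 102 patients per group are needed to reach statistically significant results also during long-term follow-up". The Discussion repeats the claim and fixes the time point: "the sample size is estimated to reach statistically significant results at the long-term follow-up at 5 years".

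The Outcomes section says how hernias are looked for at that visit: "There will be clinical evaluation without CT scan to detect any clinical PSH as long-term follow-up at 5 years after surgery". Table 1 marks CT findings at 1 and 3 years only. In the list of secondary outcomes, CT-detected PSH stops at 3 years. The 5-year hernia entries are clinically detected PSH and survival free of an operation for PSH.

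The Background treats the two detection methods as different measurements. It says that clinical examination reveals only part of what CT shows. For patients with a mesh it reports: "Clinically detected hernias are present in up to 10.6–16.4% of patients with a parastomal mesh", against 32.4–36.6% on CT. For the case series of 31 patients with the trial mesh it reports: "the incidence of PSHs was clinically found 3.2% and in CT scans 6.4% at the 1-year follow-up".

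**The concern.** A power statement holds for one endpoint, one time point and one pair of rates. Here the effect size belongs to CT at 12 months, and the claim is made for a visit without CT. Keeping 51 evaluable patients per group at 5 years preserves the 90% power only if the 5-year outcome has rates about as far apart as 6.4% and 34%. The article offers no reason to expect that for clinical detection, and its own figures point to lower rates at 1 year.

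The claim is also the stated reason for enrolling 102 rather than 51 per group, and long-term results are a declared focus of the trial. If the 5-year comparison is not significant, readers who were told that the trial was sized for significance there may conclude that the benefit has faded. A less sensitive endpoint in half the patients could produce the same result.

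**Working it through.** **Inputs from the protocol article.** Planning rates 6.4% (mesh) and 34% (control), CT, 12 months; α = 0.05; power 90%; 51 per group; 5-year drop-out 50%; 102 per group (Sample size). Allocation is "randomized at a ratio of 1:1 by browser-based software" (Abstract). Clinical and CT rates come from the Background. A two-sided test is assumed, because the article does not state the sidedness.

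**1. Reproducing the plan's figure.** With p̄ = (0.064 + 0.34)/2 = 0.202, the pooled normal formula is

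n = [1.960·√(2·p̄(1−p̄)) + 1.282·√(p₁(1−p₁) + p₂(1−p₂))]² / (p₁−p₂)²

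= (1.113 + 0.683)² / 0.0762 = 42.4, so 43 per group.

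With continuity correction this becomes 49.3, so 50 per group, within one patient of the stated 51. Attrition: 51/(1 − 0.5) = 102, as stated. The arithmetic is sound for the CT endpoint.

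**2. Power at the planning rates.** Exact power here sums the binomial probabilities of all tables in which the two-sided chi-square test without continuity correction rejects. For 6.4% vs 34% it is 0.96 with 51 per group (Fisher's exact test 0.93) and above 0.999 with 102 per group.

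**3. Clinical-to-CT ratios.** All come from patients with a mesh:
- 10.6/32.4 = 0.33
- 16.4/36.6 = 0.45
- 3.2/6.4 = 0.50

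The first two pair the low ends and the high ends of two ranges. The article does not say which clinical figure goes with which CT figure; crossed pairing gives 10.6/36.6 = 0.29 and 16.4/32.4 = 0.51.

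**4. Sensitivity of power for clinical detection, 51 per group.** No clinical rate is given for controls without mesh, so every control rate below is an assumption.

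| Mesh vs control | Origin of the rates | Exact chi-square | Fisher |
|---|---|---|---|
| 2.1% vs 11.1% | ratio 0.33 on both planning rates | 0.45 | 0.26 |
| 2.9% vs 15.2% | ratio 0.45 on both | 0.61 | 0.44 |
| 3.2% vs 17% | ratio 0.50 on both | 0.68 | 0.52 |
| 3.2% vs 11.1% | mesh from the PVDF series, control by ratio 0.33 | 0.33 | 0.18 |
| 3.2% vs 25% | assumed higher 5-year control rate | 0.93 | 0.87 |
| 6.4% vs 25% | mesh rate higher as well | 0.76 | 0.66 |
| 10.6% vs 25% | mesh at the low end of the meta-analysis range | 0.48 | 0.38 |

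Fisher's test is shown because the Statistical methods section allows either test.

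**5. Reading the table.** The first four rows carry 1-year rates to 5 years. The last three allow for growth over time, which the Background says occurs. A higher control rate restores about 90% power if the mesh rate stays near 3.2%, but not if the mesh rate rises too.

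**The case against.** The strongest case against the point concerns its size. A reader might infer that the trial has only about 33–68% power at 5 years on the article's own rates. The documents do not support that. They give no clinically detected rate for patients without mesh and no 5-year clinical rate for either group. The 10.6–16.4% refers to patients with a mesh. The ratio of 0.50 comes from 31 patients, where 3.2% and 6.4% are 1 and 2 hernias. The 0.33 figure mixes two ratios, scaling the control arm by 0.33 while leaving the mesh arm at the 0.50 ratio; one ratio for both arms gives 0.45 as the lowest value. Using 1-year rates at 5 years also carries a rate across time points, and the Background says that incidence grows and cites up to 81% after long follow-up. All of this stands: the power is undetermined, not shown to be low.

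Two further objections stand in part. Clinical detection is not the only 5-year hernia outcome, since survival free of an operation for PSH is listed too, but the sample size was not calculated for that outcome either. The Statistical methods section names PSH incidence at 5 years without restricting it to clinical detection, so a cumulative incidence that counts earlier CT findings is not ruled out. However, the outcome list names the 5-year incidence as clinically detected, and no cumulative analysis is described.

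Finally, the 5-year outcome is secondary and the 12-month primary comparison is amply powered at the planning rates. That limits the consequence but does not make the 5-year claim correct.

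**Conclusion.** The point holds as an endpoint mismatch in the sample size justification. It is not an arithmetic error: 51 and 102 both reproduce. The claim that 102 per group reaches significance at 5 years has no calculation behind it for the outcome assessed at that visit.

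Its size cannot be fixed from the document. Under the labelled assumptions, power with 51 per group is about 0.45–0.68 when one clinical-to-CT ratio of 0.33–0.50 is applied to both 1-year planning rates. With an assumed 25% control rate it is 0.93, 0.76 or 0.48 for mesh rates of 3.2%, 6.4% or 10.6%. These are exact chi-square values with two-sided α = 0.05 and exactly half the patients evaluable; Fisher's test gives less. The range includes values near the planned 90% and values about half of it, which is why significance at 5 years should not be asserted. The primary analysis at 12 months is unaffected.

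**What to change.** - **Sample size section:** state that the 90% power and the 51 per group refer to CT-detected PSH at 12 months only. Do not attach the 90% to 102 per group, where power at the planning rates exceeds 99.9%.
- **Sample size section and Discussion:** remove the claim that the sample size reaches significance at 5 years. Say instead that 102 per group is meant to leave about 51 evaluable per group at 5 years if half drop out. Give the power for clinically detected PSH as a range, with the assumed rates shown.
- **3-year CT:** make no power claim unless 3-year planning rates are stated, since the article has none.

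The 5-year comparison may still be tested as a secondary outcome; it need not become estimation only. The change is to wording, enrolment stays at 102 per group, and the cost is a less favourable stated figure for long-term power.
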